**Methods:**

Double-blind randomized controlled trial of patients with diffuse axonal injury. Thirty-six patients will be randomized to either an active coil group or sham group in a 1:1 ratio. rTMS protocol: 10 sessions of high-frequency rTMS (10 Hz) over the left dorsolateral prefrontal cortex (DLPFC). Cortical Excitability measures will be obtained. Neuropsychological evaluations will be performed 1 week before, 1 week and 3 months after rTMS. There are 2 study hypotheses: (1) rTMS over the left DLPFC in patients with DAI will improve cognitive function and (2) whether rTMS is safe in TBI patients.

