### Study purpose and objectives

The clinical goal is to assess safety and determine whether high-frequency rTMS of the left dorsolateral prefrontal cortex (DLPFC) is effective for the cognitive rehabilitation of DAI patients after TBI.

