### Safety considerations and adverse events

This protocol is in accordance to the most recent guidelines about rTMS reported by Rossi et al. [31].

As per each meeting, patients will be questioned about adverse events and the information will be recorded and published. If a major adverse event occurs (e.g. seizure), the subject will receive medical assistance and further examination and investigation will be provided as needed. Family members will receive a feedback on the status of their relative who is enrolled in the study, and a contact number of the investigators and TMS clinic will be provided for further questions.

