**Fig. 2 Fig2:**
[figure not shown]
Study flow diagram: this study will recruit 36 patients from Hospital das Clínicas, University of São Paulo, Brazil. After baseline data collection, participants will be randomized to active coil group or sham coil group in a 1:1 ratio. Baseline assessment include standard history and clinical assessment, neurocognitive evaluation, prevalence of pain symptoms (assessed with the VAS, DN4, and The McGill Pain Questionnaire), MRI scan, and cortical excitability assessment with TMS. After the end of the intervention (rTMS), participants will undergo two revaluations (early and late data collection). DN4,*Douleur Neuropathique* 4, MRI, magnetic resonance imaging, TMS, Transcranial Magnetic Stimulation, rTMS, repetitive TMS, VAS, visual analogic scale

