### Data analysis

The SPSS 19.0 software package for Windows (SPSS Inc., Chicago, IL, USA) will be used for all statistical analyses. The *T* test will be used for comparison between means and Chi-squared test for proportions. Non-parametric analysis will include Wilcoxon and Mann–Whitney tests. A significance level of *p* < 0.05 will be chosen for all tests. A fully specified statistical analysis plan will be written before unmasking the study in order to guarantee replicability and to avoid outcome selective reporting. All the analysis will be based on “as randomized” patients.

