### Sample size

We have considered a difference of 1 standard deviation in TMTB, an 80 % power, and an alpha of 5 %, a minimum of 15 participants are needed for each group. We will add three patients per group to compensate for possible loss of follow-up. Thereafter, 18 patients will be allocated to each group.

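### The as-randomized rule is written for every analysis, complications included; it should be limited to efficacy, because it can understate harm if a patient never starts rTMS or receives the wrong coil

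*Protocol article*

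**What the plan says.** The Data analysis section lists the tests, including a chi-squared test for proportions, and promises that "A fully specified statistical analysis plan will be written before unmasking the study". It then closes with "All the analysis will be based on “as randomized” patients". No safety set or treated set is named, and complications are not excepted.

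Safety is prominent elsewhere in the article. The Abstract gives the second hypothesis as "2) whether rTMS is safe in TBI patients". Study purpose and objectives says "The clinical goal is to assess safety and determine whether high-frequency rTMS" is effective. Secondary outcome measures lists complications first. Under Safety considerations and adverse events, "patients will be questioned about adverse events and the information will be recorded and published", with seizure given as the example of a major event.

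Two design facts bear on the point. The legend to Fig. 2 places allocation ahead of treatment: "After baseline data collection, participants will be randomized to active coil group or sham coil group in a 1:1 ratio". The Sample size section allows for attrition: "We will add three patients per group to compensate for possible loss of follow-up".

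**The concern.** Analysing by assigned arm protects an efficacy comparison, because departures from the assigned treatment usually shrink the difference and so work against a false claim of benefit. For harms the same shrinkage works in favour of the treatment. A patient assigned to active rTMS who never has a session cannot have a complication of it, yet still enlarges the denominator. A complication after active stimulation in a patient assigned to sham would be counted against sham.

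The article states this rule; it does not leave the matter open. A later analysis plan with a treated-patient safety set would contradict the sentence, and a plan that followed the sentence would carry the weakness into the safety results. With 18 patients per arm and serious events expected to be rare, one patient in the wrong row or one surplus denominator is visible in the table.

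**Working it through.** **The plan's own figures.** For a 1 SD difference, 80% power and 5% two-sided alpha, the normal approximation gives 2 × (1.960 + 0.842)² = 15.7, so 16 per group. The t-test version gives 17. The stated minimum of 15 is close to these. Adding 3 gives 18, and 15/(1 − 3/18) = 18 agrees. Nothing below depends on whether the minimum is 15, 16 or 17; only the 18 per arm is used.

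**Inputs.** From the article: 18 per arm (Randomization and blinding; Sample size) and an allowance of 3 losses per arm (Sample size). Assumed, because the article gives no figure:
- *u*, the number of active-arm patients who never have an rTMS session
- *c*, the number of patients per arm who receive the other coil throughout
- no complications recorded in patients who never start

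**Never-started patients.** Observed active-arm risk = true risk in treated patients × (18 − u)/18.

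| u | (18 − u)/18 | Relative understatement | Observed risk if the true risk is 20% (assumed) |
|---|---|---|---|
| 0 | 100% | 0% | 20.0% |
| 1 | 94.4% | 5.6% | 18.9% |
| 2 | 88.9% | 11.1% | 17.8% |
| 3 | 83.3% | 16.7% | 16.7% |

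The row u = 3 is an extreme: it takes the whole loss allowance and places it before the first session. In that case one event reads as 1/18 = 5.6% instead of 1/15 = 6.7%. With no events, the one-sided 95% upper limit is 1 − 0.05^(1/18) = 15.3% instead of 1 − 0.05^(1/15) = 18.1%.

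The between-arm difference shrinks in the same proportion if u is equal in both arms. If u differs between arms the difference can move either way, because never-started sham patients lower the sham risk as well.

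**Wrong coil.** With c patients crossed in each direction, observed difference = true difference × (1 − 2c/18). One crossing each way shrinks it by 11%, two by 22%, none by 0%.

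For a single event, suppose one patient assigned to sham receives the active coil and has the only event of the trial.
- By assignment: 0/18 active v 1/18 sham, a difference of −5.6 points.
- By coil received: 1/19 active v 0/17 sham, a difference of +5.3 points.

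The two tables differ by about 11 points and have opposite signs.

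**The case against.** The strongest reply is that this is detail for the statistical analysis plan. The sentence just before the rule defers full specification to that document, the article is a condensed account, and the rule reads like a general intention-to-treat statement that does not mention complications. This would answer a complaint that no safety set is defined. It does not fully answer a sentence that says all analyses and would have to be contradicted to do the usual thing. It does keep the point small.

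Several stronger readings are tempting and are not supported:

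- *That the active-arm risk is in fact diluted.* The article reports no patient who was randomized and not treated, and none who received the wrong coil. Without either, the two ways of counting give the same table.
- *That coil mix-ups are likely.* The Magnetic stimulator section names separate active and sham coil models of the same size and shape, but does not say how or by whom they are changed. Randomization and blinding has the two authors who apply rTMS assign the interventions and does not list them as blinded, which makes an unnoticed swap less likely.
- *That three patients per arm will leave before treatment.* The allowance is for loss to follow-up, which runs to 90 days. Such losses can occur after stimulation, and those patients belong in the safety denominator under either rule.
- *That stated risk limits will be too tight.* The article plans no confidence limits for complications. The 15.3% and 18.1% above only illustrate what the denominator does.

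It is also fair to say that the rule fixes the grouping of patients and does not expressly fix the denominator. Keeping never-started patients in it is the natural reading, not the only one.

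**Conclusion.** The point holds as a wording fault with a conditional effect. Read literally, the rule covers complications, groups them by assigned coil and most naturally counts every randomized patient. If a patient never starts or receives the wrong coil, the active-arm risk or the between-arm difference can be biased towards no harm. The size is about 5.6% relative for each never-started active patient of 18, and 16.7% if the whole loss allowance fell before the first session. With full delivery of the assigned coil it is zero. The values of u and c are assumptions, and the article gives no ground for expecting any particular value. The correction is still worth making, because safety is a named hypothesis, the arms are small, and the change can be made before unmasking without knowledge of the results.

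**What to change.** Limit the closing sentence of Data analysis to efficacy, and add a sentence such as: *Complications will be tabulated for all patients who received at least one rTMS session, by coil received; a patient who received at least one active session is counted as active, and the number of sessions received is shown.*

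Two details matter. The condition should be an rTMS session, not any stimulation, because the Cortical excitability section schedules TMS measurements before treatment. The rule for a patient who received both coils is needed because grouping by coil received would otherwise leave that patient unclassified.

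The coil used at each session should be on the session record; the article does not say whether it already is. The analysis plan should carry the same definition.

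The cost is one added sentence, one line on the record if it is not there now, and a safety denominator that may be slightly smaller than 18 per arm. Sample size and the efficacy analysis are unchanged.

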### Sample size

We have considered a difference of 1 standard deviation in TMTB, an 80 % power, and an alpha of 5 %, a minimum of 15 participants are needed for each group. We will add three patients per group to compensate for possible loss of follow-up. Thereafter, 18 patients will be allocated to each group.

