#### Randomization and blinding

Randomization will be done via a computer-produced randomized controlled table. Thirty-six patients will be randomized in 1:1 ratio into 2 groups: active coil group and sham coil group. This is a double-blind study, which the neuropsychologists and the patients (as well as their relatives) will be blinded for the group assignment. Only two of the authors involved directly with the rTMS application will assign participants to interventions.

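### The stated minimum of 15 per group falls short of 80% power for a 1-SD difference; a two-sided t-test needs 17 evaluable per group and has 75% power at 15

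*Protocol article*

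**What the plan says.** The Sample size section of the protocol article gives its inputs in one sentence: "We have considered a difference of 1 standard deviation in TMTB", with 80% power and 5% alpha. It concludes that "a minimum of 15 participants are needed for each group". It continues: "We will add three patients per group to compensate for possible loss of follow-up", so that "18 patients will be allocated to each group". The Randomization and blinding section agrees with that total: "Thirty-six patients will be randomized in 1:1 ratio into 2 groups".

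On the test, the Data analysis section says that the t "test will be used for comparison between means and Chi-squared test for proportions", and adds: "Non-parametric analysis will include Wilcoxon and Mann–Whitney tests". It does not say which of these applies to TMTB. On the significance level it says: "A significance level of *p* < 0.05 will be chosen for all tests". Neither section states whether tests are one- or two-sided, or whether the 1 SD is that of the raw score or of the change from baseline. The Primary outcome measures section frames the primary hypothesis as improvement from baseline to the early assessment, active against sham.

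**The concern.** The inputs are simple enough to check by hand, and they do not lead to 15. The word minimum claims that 15 evaluable patients per group reach 80% power. The loss allowance is then built on 15, so any shortfall there carries into the 18.

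This is the only power statement for the primary outcome. If the trial ends with about 15 evaluable per group and a null result, readers would take the chance of missing a true 1-SD effect to be 20%. On the usual two-sided reading it would be about 25%. The Discussion section says that the results should help to design larger trials, so the stated power is likely to be relied on.

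**Working it through.** **Inputs.** Standardised difference d = 1, power 80%, alpha 5%, 15 per group and an allowance of 3 per group (Sample size); 1:1 allocation (Randomization and blinding); t-test for means (Data analysis). Two assumptions are needed because the article is silent: the test is two-sided, and 1 SD is the SD of the variable compared between groups.

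**Step 1: reproduce the plan's figure.** The two-sided normal approximation is n = 2(z₀.₉₇₅ + z₀.₈₀)²/d² = 2(1.960 + 0.8416)² = 15.70 per group. Rounded up, this is 16; rounded down, it is the stated 15. By the same approximation, power is 78.2% at 15 and 80.7% at 16. So the origin of 15 can be seen, but even its own formula does not reach 80% there.

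**Step 2: two-sided t-test.** Power comes from the noncentral t distribution with 2n − 2 degrees of freedom and noncentrality d√(n/2). At n = 15 the noncentrality is √7.5 = 2.739, with 28 degrees of freedom and critical value 2.048.

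| Evaluable per group | Losses per group from 18 | Power |
|---|---|---|
| 15 | 3 | 75.3% |
| 16 | 2 | 78.1% |
| 17 | 1 | 80.7% |
| 18 | 0 | 83.0% |

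Solving for 80% gives n = 16.71, so 17 per group. With 15 per group, the difference detectable with 80% power is 1.06 SD.

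**Step 3: one-sided 5% test.** The normal formula gives 12.37, so 13. The exact t-test gives 13.10, so 14. Power at 15 is 84.8% by the t-test. On this reading 15 is enough, but it is still not the minimum.

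**Step 4: Mann–Whitney, if it were the test for TMTB.** With normal data, power at 15 is about 72% by simulation and about 73% by the asymptotic relative efficiency of 0.955. At 18 it is about 80% and 81%. This is a side check, because the article does not assign that test to TMTB.

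**Step 5: which SD.** Let r be the correlation between baseline and follow-up TMTB, which the article does not give. If 1 SD is the raw-score SD and change scores are compared, the SD of change is √(2(1 − r)) raw SDs, so the effective d is 1/√(2(1 − r)). Two-sided power at 15 per group is then 60.8% at r = 0.3, 67.5% at 0.4, 75.3% at 0.5 and 84.0% at 0.6; it reaches 80% at r of about 0.56. With baseline adjustment (ANCOVA) the effective d is 1/√(1 − r²), and power at 15 is 79.1% at r = 0.3 and 82.2% at r = 0.4. It passes 80% between these: at r = 0.35 it is about 80.5%.

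**The case against.** The best defence is that 15 is close to a recognised answer. It is the standard two-sided normal formula truncated, one patient per group below the correctly rounded value, and no input is wrong. That stands as an explanation, and it makes the error small. It does not make 15 a minimum, since the formula itself gives 78.2% there.

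Second, the article states neither sidedness nor which SD is meant. A one-sided 5% test gives 84.8% at 15, and a raw-score SD with a high enough baseline correlation also lifts power above 80%. This too stands: the 75% is conditional and must be presented so. Two-sided is, however, the usual reading of an unqualified 5% level, and nothing in the article declares a one-sided test. On the raw-score reading, a correlation below 0.5 makes change-score power worse than 75%.

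Third, a reader might infer that the trial as designed lacks 80% power, or that 15 is the number expected to be analysed. The article supports neither. It randomises 18 per group, where power is 83.0%, and the three extra patients are an allowance for losses that may or may not occur. The shortfall appears only if losses exceed about one per group. A reader might also take the gap as serious enough to invalidate the design. A gap of about 5 points of power, or two evaluable patients per group, does not support that.

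**Conclusion.** The stated minimum is wrong as written, because no standard calculation tried gives 15 as the smallest size reaching 80%. For a two-sided 5% two-sample t-test, with 1 SD referring to the analysed variable, the minimum is 17 − 15 = 2 patients per group higher. If the whole loss allowance is used, power is about 5 points below the claim. With equal losses in the two groups, the claim holds up to one loss in each. The conclusion about power at 15 rests on those two unstated assumptions and would reverse under a one-sided 5% test; the conclusion that 15 is not the minimum holds under either sidedness. Severity is minor to moderate: the planned 18 per group can stand, and no analysis or allocation changes.

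**What to change.** Keep 18 per group and restate the Sample size paragraph along these lines: 18 patients per group will be randomised; for a two-sided two-sample t-test at 5% and a difference of 1 SD (naming the SD: raw TMTB score or change from baseline), 17 evaluable per group are needed for 80% power; power is 83% with no losses and 75% if only 15 per group are evaluable. If a one-sided test was intended, say so and give its figures instead (14 needed, 85% at 15).

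Alternatively, base the calculation on a baseline-adjusted comparison of early TMTB. With 1 SD as the raw-score SD, this reaches 80% at 15 per group if the baseline to follow-up correlation is at least about 0.35. The article gives no such correlation, so it must be stated as an assumption, and the primary analysis must then be the adjusted one.

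The first option costs one corrected paragraph and a slightly less favourable stated power. The second also commits the analysis plan, which the Data analysis section says will be written before unmasking, to the adjusted model. Neither needs more patients. Holding 80% after three losses per group would instead mean 17 + 3 = 20 per group, 40 in total. Applying the implied loss rate of 3/18 gives 17/(1 − 1/6) = 20.4, so 21 per group and 42 in total. A gap of this size does not require that.

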## Discussion

It is a truism that TBI has a devastating global impact in terms of public health. Unfortunately, most of the cognitive rehabilitation strategies to date have shown only modest results. A multidisciplinary approach seems to be the most feasible intervention. Therefore, rTMS, as a non-invasive brain stimulation technique, has a particularly important appeal: the potential as a therapeutic instrument while obtaining insights into questions of brain function and pathophysiology of disabling cognitive processes. The results obtained from this study will be valuable in order to design larger randomized clinical trials and establish new concepts to the treatment of cognitive sequelae in patients with DAI.

## Trial status

This trial was registered on the website clinicaltrials.gov with the registration number NCT02167971. At the writing of this paper, we have already performed rTMS on nine patients and we are still recruiting subjects. The study began in January 2014 and the programmed completion date for the primary outcome is September 2015.

## Abbreviations

BDI-II: Beck Depression Inventory
BVMT: Brief Visuospatial Memory Test
CONSORT: Consolidated Standards of Reporting Trials
DAI: diffuse axonal injury
DN4: *Douleur Neuropathique* 4
DLPFC: dorsolateral prefrontal cortex
HVLT: Hopkins Verbal Learning Test
ICF: intracortical facilitation
ISI: interstimulus interval
MRI: magnetic resonance imaging
RMT: resting motor threshold
rTMS: Repetitive Transcranial Magnetic Stimulation
SICI: short-interval cortical inhibition
SPIRIT: Standard Protocol Items: Recommendations for Interventional Trials
STAI: State-Trait Anxiety Inventory
TBI: traumatic brain injury
TMS: Transcranial Magnetic Stimulation
TMTA: Trail Making Test part A
TMTB: Trail Making Test part B
VAS: visual analogic scale
WAIS: working memory (subscale of Wechsler Memory Scale)
